### **6.3.3 Sensitivity analysis of primary outcome**

To evaluate the robustness of the main analysis with respect to the assumptions on missingness, an alternative multiple imputation model will be applied for sensitivity analysis. It will impute the outcomes that are missing due to study withdrawal such that outcomes in the IND and AUT arms are assumed to be similar to those observed in the TAU group. The details will be fixed in the statistical analysis plan.

To evaluate the robustness of the comparison of IND versus AUT in the main analysis with respect to adherence, the main analysis will be repeated in subpopulations of adherent caregivers. Non-inferiority will be concluded if the lower limit of the corresponding two-sided 95%-confidence interval for the difference of mean K-10 changes from baseline (IND minus AUT) is greater than -0.62 points. The details will be fixed in the statistical analysis plan.

#### **6.3.4 Supplementary analysis of primary outcome**

In order to assess the consistency of the treatment effect in relevant subgroups (EMA-CHMP, 2019), exploratory analyses will be performed using all variables for grouping that were used for stratified randomization (i. e. age, gender, relation with depressed person, pre-intervention (T0) K-10 score) as well as internet literacy.

Further analyses will explore possible moderators (measured at baseline, e. g., possible effects of features of the depressed person such as duration of illness or type of relation with the depressed person) and mediators (e. g. adherence to randomized interventions, importance of changes in interaction behaviour for treatment effects on participants K-10 scores) on primary and secondary outcomes. These analyses will be conducted as part of PhD theses and will be pre-specified elsewhere at a later time.

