## **5 Methods: Assignment of interventions**

### **5.1 Allocation**

#### **5.1.1 Sequence generation**

For allocation to the intervention and control groups IND, AUT and TAU, a computer-generated random list with a 2:2:1 ratio is used, with stratification based on the participating caregivers characteristics as follows:

- age (years, 18-40, 41-65,  $\geq 66$ )
- gender (female, male, diverse)
- relation with depressed person (parent, child, partner, other)
- K-10-scale (10-22, 23-50).

These characteristics were selected because each variable could plausibly influence participants' response to the interventions. The K-10 cut-off value was chosen based on its ability to differentiate healthy persons from persons at risk of a mental disorder in the German validation study (Giesinger, Rumpold, & Schüßler, 2008). Details of the randomization algorithm will be documented separately and will not be disclosed to the participants.

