### **6.3.2 Main analysis of primary outcome**

**Model:** The primary efficacy analysis will be performed in the full analysis set (FAS) according to the intention-to-treat (ITT) principle. Therefore, all randomized caregivers will be analysed in the assigned treatment arms, irrespective of treatment adherence and whether they refuse or discontinue the intervention. The effects of allocation to IND, AUT and TAU with respect to the primary endpoint, change in K-10 score from baseline to four weeks after randomisation, will be estimated and tested in a linear regression model, and the corresponding two-sided 95%-confidence intervals will be reported. The model will include randomized treatment (IND, AUT, TAU), age (years, 18-40, 41-65,  $\geq 66$ ), gender (female, male; for diverse, see end of paragraph), caregiver's relation with depressed person (parent, child, partner, other), and K-10 baseline scores as independent variables. Since very few caregivers of diverse gender are expected, they will be assigned alternately to the groups of females and males in the primary analysis of intervention effects. They will be analysed separately in secondary analyses exploring the effect of gender.

**Sequential testing:** Following a sequential closed testing procedure to ensure a multiple type I error rate of 5%, confirmatory comparisons of randomized treatment arms will proceed until the first occurrence of a non-significant result at the nominal 5% level, followed by descriptive reporting of all subsequent analyses. The two-sided tests of equality of means of two treatment arms will be based on the two-sided 95% confidence interval for the difference in mean change from baseline estimated from the linear regression model. Treatment arms will be compared in the following order: IND versus TAU, AUT versus TAU, IND versus AUT. Although it is hypothesized and subjected to confirmatory testing that IND is superior to AUT, equality is also deemed possible. In a secondary descriptive analysis, demonstration of non-inferiority of AUT compared to IND will also be attempted. If the lower limit of the two-sided 95%-confidence interval for the difference of mean K-10 changes from baseline (IND minus

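### Consistency of effect over baseline K-10: add an exploratory treatment-by-score term in Section 6.3.4 beside the banded estimates, as bands alone may waste information

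*Protocol*

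**What the plan says.** Protocol 6.3.4 (Supplementary analysis of primary outcome) sets out how consistency of the effect will be assessed: "exploratory analyses will be performed using all variables for grouping that were used for stratified randomization". The variables listed include "pre-intervention (T0) K-10 score) as well as internet literacy". Section 6.3.4 gives no cut-off for K-10.

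The cut-off comes from 5.1.1 (Sequence generation), which lists "K-10-scale (10-22, 23-50" as the two bands for stratification. The cut was chosen for its "ability to differentiate healthy persons from persons at risk of a mental disorder in the German validation study". On the stratification variables in general, 5.1.1 says: "These characteristics were selected because each variable could plausibly influence" how participants respond to the interventions.

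The primary regression in 6.3.2 uses the full score, naming "K-10 baseline scores as independent variables", while age enters in three bands.

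The next paragraph of 6.3.4 continues: "Further analyses will explore possible moderators (measured at baseline, e. g". Its examples are open-ended and do not mention the T0 K-10. Those analyses are left to doctoral work and to a later document. Section 6.3.5 applies the same subgroup approach to the secondary outcomes.

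**The concern.** The K-10 runs from 10 to 50 (6.1.2). Grouping at 22/23 treats caregivers scoring 22 and 23 as different and those scoring 23 and 50 as alike. The plan uses the whole score to adjust the main effect but, in its stated consistency assessment, appears to fall back on two bands to look for effect modification.

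Baseline distress is one of the more plausible modifiers here: 5.1.1 selected it for that reason, and 3.3 makes finding moderators a secondary goal. If benefit rises or falls gradually with baseline distress, a two-band comparison estimates that gradient less precisely than the score would. A real gradient could then look like consistency.

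**Working it through.** **The plan's own figures.** These are reproduced first, because the same inputs are used below.
- IND or AUT against TAU with 400 and 200 outcomes (4.6): the standard error of a standardised difference is √(1/400 + 1/200) = 0.0866. For d = 0.3, 0.3/0.0866 = 3.46 and Φ(3.46 − 1.96) = 93%, as stated.
- IND against AUT with 400 and 400: 0.2/√(2/400) = 2.83 and Φ(2.83 − 1.96) = 81%, as stated.
- SD of change with K-10 SD 6.2 and correlation 0.5 (6.3.2): √(2 × 6.2² × 0.5) = 6.2, as stated.

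The protocol states no power or precision for any interaction.

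**Information kept by two bands.** Assume a normal T0 score and an effect linear in it. With share p of caregivers below the cut, the efficiency of the split relative to the full score is φ(z_p)² / [p(1 − p)].

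| Split | Calculation | Kept | Lost |
|---|---|---|---|
| 50/50 | 0.3989² / 0.25 | 0.637 | 36% |
| 70/30 | 0.3477² / 0.21 | 0.576 | 42% |
| 80/20 | 0.2800² / 0.16 | 0.490 | 51% |

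The split is not given. With SD 6.2 and the cut at 22.5, the loss is 36% at an assumed mean of 22.5, 40% at 20 or 25, 48% at 18 or 27, and 58% at 16 or 29. So 36% to 51% is an illustrative range, not a bound.

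**What this means for detection, IND against TAU.** With correlation 0.5, the residual SD after adjustment for baseline is √(1 − 0.5²) = √0.75 of the K-10 SD. The standard error of the interaction slope, in SD of outcome per SD of baseline, is √0.75 × 0.0866 = 0.075. Power is Φ(slope/0.075 − 1.96). For the bands, slope/0.075 is multiplied by the square root of the efficiency. The gradients are assumed.

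| Gradient | Full score | Bands 50/50 | Bands 70/30 | Bands 80/20 |
|---|---|---|---|---|
| 0.20 | Φ(2.67 − 1.96) = 76% | Φ(2.13 − 1.96) = 57% | Φ(2.02 − 1.96) = 53% | Φ(1.87 − 1.96) = 46% |
| 0.15 | Φ(2.00 − 1.96) = 52% | Φ(1.60 − 1.96) = 36% | Φ(1.52 − 1.96) = 33% | Φ(1.40 − 1.96) = 29% |

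Both SDs are 6.2, so a gradient of 0.20 means that the arm difference changes by 0.20 K-10 points per baseline point.

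A simulation with rounded scores bounded at 10 and 50, residual SD √0.75 and gradient 0.25 agrees with the formula. The bands reach 76%, 70% and 64% with 50%, 30% and 20% of caregivers below the cut (formula 76%, 72%, 65%), and the full score reaches 90% to 92% (formula 92%).

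**The reverse case.** Suppose the effect is flat within each band and jumps by 0.35 SD at the cut, with a 50/50 split. The standard error of the between-band difference is 0.075/√0.25 = 0.15, so the bands have power Φ(2.33 − 1.96) = 65%. The linear term has Φ(2.33 × 0.798 − 1.96) = Φ(−0.10) = 46%. Here the bands are the better tool.

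**The case against.** The strongest reply is that this is detail for the SAP, which is not at hand. Section 6.3.4 names variables but gives no model form, and nothing stops the SAP from adding a continuous term. That explains why the point is small. It does not remove it, because 6.3.4 does state grouping as the method and names no other for this purpose.

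Several stronger readings are tempting, and the documents do not support them:
- A reader might infer that baseline K-10 will be examined only in bands. The moderator paragraph has an open list of baseline variables. One of its examples, the type of relation, is itself a stratification variable, so K-10 could well be included. It is simply not named, and the specification is deferred.
- A reader might take the bands in 6.3.4 as stated. They are inferred from 5.1.1, although no other K-10 grouping appears.
- A reader might take 36% to 51% as an established loss. It depends on a normal score, a linear gradient and an assumed split. The cut was chosen to separate healthy from at-risk persons, so a step there is possible, and then the bands lose nothing.
- A reader might extend the argument to age. Age enters the primary model in bands (6.3.2), so the reasoning that the full variable is already in the model does not carry over.

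It is also fair that the analyses are exploratory, that 6.3.1 puts intervals ahead of p-values, and that no rule turns a non-significant subgroup result into a claim of consistency. The power figures therefore illustrate precision and do not describe a decision in the plan. Even the full score gives only 52% to 76% power at the assumed gradients.

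**Conclusion.** The point holds as a low-cost improvement, not as an error. The stated consistency assessment groups on T0 K-10, the only grouping available is 10-22 against 23-50, and the score itself is already in the primary regression. Under a roughly normal score and a linear gradient, the bands alone lose about 36% of the information at a 50/50 split and 51% at 80/20. The loss is larger for more uneven splits and absent for a true step at the cut. Neither approach is best in every case, which is the reason to report both. The confirmatory tests in 6.3.2 are not affected.

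**What to change.** In 6.3.4, add an exploratory analysis that puts a treatment-by-continuous-T0-K-10 term into the primary regression, fitted in each imputed data set and combined as in 6.3.2. With three arms this is two coefficients. Report them with 95% confidence intervals, together with the estimated IND-TAU, AUT-TAU and IND-AUT differences at a few K-10 values chosen in advance. Keep the 10-22 and 23-50 estimates beside them as a display and as a check for a jump at the cut-off.

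The cost is one sentence and one model term, with no new data. The downside is the linearity assumption, which the retained banded estimates help to check.

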#### **6.3.5 Analysis of secondary outcomes**

Secondary outcomes at T2, four weeks after randomization, and T3, three months after randomization, will be evaluated in a linear mixed model per outcome scale, with a compound symmetry covariance matrix to account for correlation between T2- and T3-outcomes of the same caregiver or depressed person. Independent variables will be those of the main primary analysis, plus time point (T2, T3). The details will be fixed in the statistical analysis plan.

Subgroup analyses, moderator and mediator analyses will be performed as described for the primary outcome above.

Furthermore, the results seen in the Facing Depression Together trial will be compared to historical controls of face-to-face psychoeducation groups for caregivers of depressive in-patients from the multicentre SCHILD study (Frank, Wilk, et al., 2015).

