### Secondary outcomes:

All outcomes are to be assessed at post-intervention (T2) and at 3-month follow-up (T3)

- The subjective und objective psychosocial burden of caregiving (involvement evaluation questionnaire / IEQ-EU)
- The subjective symptom burden (symptom checklist short version / SCL-K-9)
- The depression literacy (depression literacy test; D-Lit)
- High expressed emotion aspects “critical comments” and “over-involvement” (Familienfragebogen; FFB)
- The well-being (WHO-5) of the caregivers
- Depressive symptoms in the depressed person (patient health questionnaire PHQ-9).

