**Symptom checklist 9-item short version:** The psychological burden on caregivers of mentally ill people was assessed by the German version of the SCL-K-9 (Klaghofer, R., Brähler, 2001) a shortened version of the Symptom Checklist 90-R (Derogatis, 1977; Franke, 1992). By using nine items on a five-point Likert scale ranging from 0 (not at all) to 4 (very severe), different psychological symptoms are assessed. Cronbach’s Alpha was  $\alpha = 0.87$ , which stands for a good reliability of the SCL-K-9 (Petrowski, Schmalbach, Kliem, Hinz, & Brähler, 2019).

**Depression literacy test:** The literacy concerning depression was assessed, using the German version of the Depression Literacy Test (D-Lit) (Freitag et al., 2018; english original: Griffiths, K.M., Christensen, H., Jorm, A.F., Evans, K., Groves, 2004). The D-Lit is a 35-item self-report questionnaire, assessing general information about depressive disorders, for example symptoms, impairments and treatments. Response options are “true”, “false” and “don’t know”. Reliability of the scale is reported as moderate with a Cronbachs Alpha of 0.75 (Freitag et al., 2018).

**Family Questionnaire:** The level of expressed emotion (EE) was assessed by the German version of the Family Questionnaire (FQ) (Wiedemann, Rayki, Feinstein, &

Hahlweg, 2002) a 20-item self-report questionnaire. On a four-point likert scale, ranging from “never” to “very often” caregivers of patients evaluate the frequency of specific reactions toward the patient. Internal consistency was excellent for the subscale “criticism” (Cronbachs Alpha ranging from 0.90- 0.92 depending on the sample) and good for the subscale “emotional over-involvement” (Cronbachs Alpha ranging from 0.79-0.82 depending on the sample).

**WHO-5:** The subjective psychological well-being was assessed by the German version of the 5-item World Health Organization Well-Being Index (WHO-5) (WHO, 1998). Response options are coded on a six point scale (0 = never; 5 = all of the time). The internal consistency of the German version of the WHO-5 is excellent (Cronbachs Alpha = 0.92) (Brähler, Mühlan, Albani, & Schmidt, 2007).

If the depressed person participates in the study as well, the person has to reply the following questionnaire at T0, T2 and T3:

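### As worded, the secondary-outcome models adjust every scale for the caregiver's baseline K-10 and none for its own T0 value, which costs precision

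*Protocol*

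**What the plan says.** Section 6.3.5 says that secondary outcomes at T2 and T3 "will be evaluated in a linear mixed model per outcome scale, with a compound symmetry covariance matrix". The covariates follow by reference to the primary analysis: "Independent variables will be those of the main primary analysis", plus time point. The section then adds: "The details will be fixed in the statistical analysis plan".

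The variables referred to are listed in section 6.3.2: randomised treatment, age group, gender, relation with the depressed person, "and K-10 baseline scores as independent variables".

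Section 4.4 lists the secondary outcomes as IEQ-EU, SCL-K-9, D-Lit, FFB, WHO-5 and PHQ-9; none of them is the K-10. The last is measured in another person: "Depressive symptoms in the depressed person (patient health questionnaire PHQ-9"). The table in section 6.1.2 shows every one of these scales at T0. For PHQ-9 the text adds that "the person has to reply the following questionnaire at T0, T2 and T3".

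**The concern.** For the primary outcome the plan adjusts for the outcome's own baseline. Copying the variable list by reference drops that principle for every secondary scale: the K-10 stays in, and the scale's own T0 value enters nowhere. The response is described as the T2 and T3 outcomes, and nothing in the section says that secondary scales are analysed as change.

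A scale's own baseline is normally the strongest single predictor of its follow-up value. Leaving it out widens the intervals. It also lets that part of a chance T0 imbalance which K-10 does not explain pass into the estimate. Section 6.3.1 puts the emphasis on effect estimates with 95% confidence intervals, so interval width is what the reader of the secondary results will see. PHQ-9 is the plainest case, because the depressed person's symptoms would be adjusted for the caregiver's distress.

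**Working it through.** **The plan's own figures.** No precision or power figure is given for a secondary outcome. The inputs come from the primary outcome, and these reproduce:

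- SD of K-10 change (section 6.3.2): √(2 × 6.2² × (1 − 0.5)) = 6.2.
- Power (section 4.6), normal approximation: 99.99% (stated as about 99%) for d = 0.5 and 93.4% (93%) for d = 0.3, both 400 vs 200; 80.7% (81%) for d = 0.2, 400 vs 400; 29.3% (29%) for non-inferiority.

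**Inputs for the comparison.**

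- r, correlation of a scale's T0 value with its follow-up value. The protocol gives 0.5 for K-10 only (section 6.3.2). Assumed here: 0.5, with 0.7 as a second scenario that has no source in the protocol.
- q, correlation of caregiver K-10 with the scale at T0. Not given. Section 6.1.2 reports 0.71 and 0.68 between K-10 and two related distress scales, so q is taken from 0 (plausible for D-Lit or PHQ-9) to 0.7 (plausible for SCL-K-9).
- c, correlation of baseline K-10 with the scale at follow-up. Assumed c = q × r, meaning that K-10 predicts follow-up only through the scale's own T0 value.

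**Formulas**, in units of the raw variance at one time point: residual variance with K-10 only = 1 − c²; with own T0 = 1 − r². Under c = q × r, keeping K-10 beside own T0 leaves the variance at 1 − r².

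| r | q | K-10 only | own T0 | variance ratio | interval width ratio |
|---|---|---|---|---|---|
| 0.5 | 0 | 1.000 | 0.750 | 1.33 | 1.155 |
| 0.5 | 0.5 | 0.938 | 0.750 | 1.25 | 1.118 |
| 0.5 | 0.7 | 0.878 | 0.750 | 1.17 | 1.082 |
| 0.7 | 0 | 1.000 | 0.510 | 1.96 | 1.400 |
| 0.7 | 0.7 | 0.760 | 0.510 | 1.49 | 1.221 |

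The ratios do not depend on the number of participants.

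**Check by simulation.** 4000 runs of the average of T2 and T3, complete data, r = q = 0.5, assumed T2–T3 correlation 0.6, n = 400:400:200. The standard error of IND vs TAU was 0.0750 with K-10 and 0.0641 with own T0, a variance ratio of 1.37. Averaging two visits makes the ratio larger than the 1.25 for one visit: (0.8 − 0.0625)/(0.8 − 0.25) = 1.34. The mean error was about 0 under both models.

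**Chance imbalance.** Under these assumptions the slope on own T0, given K-10, is r. A 1.96-SD imbalance in the part of T0 that K-10 does not explain, active arm vs TAU, shifts the estimate by r × 1.96 × √((1 − q²)(1/400 + 1/200)). At r = 0.5 this is 0.085 SD for q = 0 and 0.061 SD for q = 0.7. At r = 0.7 it is 0.119 and 0.085 SD.

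**If the response were change from baseline**, still with only K-10 as baseline covariate, the residual variance is 2(1 − r) − q²(1 − r)². At r = 0.5 this is 1.000 for q = 0 and 0.878 for q = 0.7, the same as in the table. At r = 0.7 it is 0.600 for q = 0, against 0.510, or 18% extra.

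**The case against.** The strongest reply is that section 6.3.5 does not name K-10. It borrows the structure of the primary model, in which K-10 is the outcome's own baseline, so the authors may have meant the baseline of the respective scale and may say so in the SAP. That may be the intention, but the sentence says something else. It names the covariate set before it defers details, and section 6.3.1 reserves for the SAP what the protocol leaves open and requires changes to be marked and justified. The wording needs correcting whichever was meant.

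Second, the response could be change from baseline, as it is for the primary outcome. Section 6.3.5 does not say so. If it were, own T0 would enter through the response, but at a correlation of 0.5 the precision loss would be no smaller.

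Third, a reader might infer that the secondary effects are biased, or that baseline imbalance is left in altogether. The documents do not support this. Allocation is randomised and stratified, including by K-10 group (section 5.1.1), so any imbalance is due to chance, and K-10 removes the share it has in common with the scale.

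Fourth, a reader might expect a loss near the upper end for all scales. The reported correlations of K-10 with related distress scales speak against that for scales such as SCL-K-9. Nor does the smaller PHQ-9 sample raise the relative loss; it lowers precision under any covariate set.

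Finally, section 6.3.1 restricts confirmatory testing to the primary outcome. That stands in full.

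**Conclusion.** The point holds on the text as written: the only baseline score in every secondary model is the caregiver's K-10, and for PHQ-9 it belongs to a different person. The consequence is lost precision and only partial removal of chance imbalance, not bias.

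At an own-baseline correlation of 0.5, with K-10 correlated 0 to 0.7 with the scale at T0, variance at a single visit is about 17–33% larger and intervals about 8–15% wider than with own-baseline adjustment. At an assumed 0.7 the figures are 49–96% and 22–40%. These figures rest on correlations that the protocol does not give for the secondary scales, and on K-10 acting only through the scale's own T0 value. The imbalance figures also use 400:400:200, which will not apply to PHQ-9 because the depressed person's participation is optional.

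No confirmatory conclusion, error rate or sample size is affected. The point is worth acting on because the remedy is cheap.

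**What to change.** State in section 6.3.5 that each secondary model includes the T0 value of the same scale in addition to the primary model's covariates. Baseline K-10 may stay, since it is a stratification factor. Say also whether the response is the score or its change from baseline.

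PHQ-9 needs a condition. Section 4.5 randomises the caregiver once the caregiver's own questionnaires are complete and does not require the depressed person's T0 PHQ-9 first. The allocation is then shown to the caregiver in an open-label trial (sections 5.1.2 and 5.2), so a T0 PHQ-9 may be missing or may be filled in afterwards. Use the depressed person's own T0 PHQ-9 only where it was completed before the caregiver's allocation was disclosed, and handle missing or late values by a stated rule such as imputation.

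The cost is a few sentences, a little extra analysis work and the handling of missing T0 PHQ-9. No new questionnaire is needed.
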